##### Part II: Renal function-related measures

2.9.2.2.

All the **baselines** mentioned below refer to data obtained within 24 h before operation.
1.Incidence of AKI within 48 h after operation. AKI is defined as current serum creatinine (SCr) increased 1.5 times baseline value OR with an increase greater than 26.5 µmol/L.2.Serum Scr, Cys C levels at 0, 24 and 48 h post operation;3.Serum NGAL levels at 0, 12, 24 and 48 h post operation;4.Arterial pH, SBE, HCO_3_^−^, Lac, Cl^−^ at 5 min post reperfusion of the donor liver, 0, 6, 12, 24 and 48 h post operation;5.Effective SID (eSID = [Na^+^] + [K^+^] + [Ca^2+^] + [Mg^2+^]-[Cl^−^]-[Lac^−^]) at 5 min post reperfusion of the donor liver, 0, 6, 12, 24 and 48 h post operation;6.Requirement of new RRT within 14 days post operation;7.RRT free and alive days to 14 days post operation.

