### Management of liver transplantation

2.8.

First, both groups received general standard of care involving the following key components (27). The operating room temperature will be set at 22°C and standard warming measures be used for all patients. All patients will receive standard general anaesthesia induced by midazolam, sufentanil, etomidate, cisatrcurium and maintained by propofol, remifentanil, sevoflurane and additional injection of sufentanil. An arterial line and a central venous catheter will be inserted before induction of anaesthesia. Mechanical ventilation will be performed routinely. During the perioperative period, all patients will receive intravenous fluids according to a standardised protocol, which includes basiliximab, antibiotics, esomeprazole and methylprednisolone. Transfusions will be administered at the discretion of the attending anaesthetist according to the National Blood Transfusion guidelines.

Throughout the operation, arterial blood gas will be measured every 60 min during the dissection phase, every 30 min during the anhepatic phase (including a 5-min pre-reperfusion blood gas) and every 30 min during the neohepatic phase for 1 h (including a 5-min post-reperfusion blood gas), then hourly until surgical closure. When pH is less than 7.2 or SBE is less than −10 mmol/L, additional 5% sodium bicarbonate will be infused with a total amount of 5% NaHCO_3_(ml) = (−2.3-SBE)*weight (kg)*0.42 to correct acidosis. The infusion will be started at a rate of 90 ml/h and discontinued with a targeted pH level of 7.35.

When the operation is completed, all the patients will be transferred to the surgical Intensive Care Units for postsurgical care. Both groups will receive standard treatment according to the guidelines after admission (27), including continuous vital signs recording, adequate fluid therapy, routine medical treatment (blood glucose control, antibiotics if needed and sedatives if required), organ support measures, etc. Organ failure would be assessed on a daily basis according to the SOFA score.

Initiation of RRT should be based on the criteria described by Bellomo et al. (28). Patients who have AKI (at least 1.5 times increase in creatinine from known baseline value) and meet predefined specific criteria will be eligible for initiation of RRT.

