#### Primary outcome measure

2.9.1.

The primary outcome measure is the change of SBE during the operation, reflected by the difference in SBE measure before and after the operation (ΔSBE = SBE_post_-SBE_pre_). SBE_pre_ will be measured before introduction of anaesthesia, and SBEpost will be measured shortly before transportation to the surgical ICU.

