##### Part I: Process measures

2.9.2.1.

1.The amount of BRS/ARS used during operation and within the first 2 days post operation;2.Additional sodium bicarbonate used during operation and within the first 2 days post operation;3.Serum acetic acid concentration before operation, 5 min post reperfusion of the donor liver, 0, 6, 12, 24 and 48 h post operation.

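### The endpoint text names no pre-operative NGAL or cystatin C value, and the stated analyses do not adjust the secondary series for baseline, which costs precision and within-patient change but not validity

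*Protocol article*

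**What the plan says.** Section 2.9.2.2 (renal function-related measures) lists, with sampling times:

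- creatinine and cystatin C: "Serum Scr, Cys C levels at 0, 24 and 48 h post operation";
- NGAL: "Serum NGAL levels at 0, 12, 24 and 48 h post operation";
- pH, SBE, bicarbonate, lactate and chloride, and separately effective SID: "at 5 min post reperfusion of the donor liver, 0, 6, 12, 24 and 48 h post operation".

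The section opens by stating that its baselines "refer to data obtained within 24 h before operation". Only the AKI definition then uses a baseline, and it uses creatinine.

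Other sections do name earlier readings. Section 2.9.2.1 lists "Serum acetic acid concentration before operation, 5 min post reperfusion of the donor liver" and later times. Section 2.9.1 says that the first SBE of the primary endpoint "will be measured before introduction of anaesthesia". Section 2.8 says that "arterial blood gas will be measured every 60 min during the dissection phase", with half-hourly gases in the anhepatic phase. Section 2.10 refers the full collection schedule to Figure 1.

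Section 2.11 names t-tests and repeated-measures ANOVA, or rank-based alternatives, for continuous outcomes. It mentions no covariate.

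**The concern.** Study fluid is given during the operation and for 48 h afterwards (section 2.7). The first listed NGAL and cystatin C readings therefore come after all the intraoperative fluid and after the graft is reperfused. They are outcomes, not baselines.

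The two markers have some weight here. Renal function is a secondary objective (section 2.1), and the Discussion concedes that the trial is not powered for AKI. Randomisation is stratified by surgical method only (section 2.5), so nothing in the design balances renal status. Section 2.4.2 excludes recent RRT and a recent rise in creatinine, but not a stable, long-standing elevation.

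If no pre-operative sample is assayed, three things are lost: precision, the ability to report change within patients, and the ability to see whether the arms started level on these markers. The Background also hopes that the results will help to power a phase III trial. The pre/post correlation and the SD of change, both useful for that, could not be estimated for NGAL or cystatin C. An analysis plan cannot recover a sample that was never taken.

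**Working it through.** **The plan's own figure.** Inputs from section 2.11: difference 1.7 mmol/L, SD 2.5 mmol/L, two-sided alpha 0.05, power 80%, loss 5%.

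n per arm = 2 × (1.960 + 0.842)² × (2.5/1.7)² = 33.95, so 34. Allowing for loss, 34/0.95 = 35.8, so 36 per arm and 72 in all. The stated size reproduces, and this point does not touch it.

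**Which analytes have a pre-operative value in the visible text.**

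| Analyte | Pre-operative value |
|---|---|
| Acetate | Yes, listed in 2.9.2.1 |
| SBE | Yes, 2.9.1 |
| Creatinine | Yes, implied by the AKI baseline in 2.9.2.2 |
| pH, bicarbonate, lactate, chloride | A gas is drawn before anaesthesia, but these values are not listed |
| Effective SID | Not listed; pre-operative Mg unconfirmed |
| Cystatin C | None found |
| NGAL | None found |

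**Chance imbalance at baseline, 36 per arm, in units of the between-patient SD.**

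- SE of the difference in baseline means = √(2/36) = 0.236; 95% range ± 1.96 × 0.236 = ± 0.46.
- P(|difference| > 0.3) = P(|Z| > 0.3/0.236 = 1.27) ≈ 0.20 for each marker.
- An imbalance of 0.3 SD moves the expected post-operative contrast by r × 0.3. This is 0.12 SD at r = 0.4 and 0.21 SD at r = 0.7, or about 0.5 and 0.9 of its own standard error (0.12/0.236 and 0.21/0.236).

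**Precision lost.** With the baseline as a covariate, the variance of the contrast is multiplied by 1 − r². The documents give no r, so the values below are assumptions. The equivalent size is 36/(1 − r²). The last two columns use 34 evaluable per arm (36 less 5%). Detectable difference = 2.802 × √(2/34 × (1 − r²)). Power at a true difference of 0.5 SD = Φ(0.5/√(2/34 × (1 − r²)) − 1.96).

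| r | 1 − r² | Equivalent n per arm | Detectable at 80% power (SD) | Power at 0.5 SD |
|---|---|---|---|---|
| No baseline used | 1 | 36 | 0.68 | 54% |
| 0.4 | 0.84 | 43 | 0.62 | 61% |
| 0.5 | 0.75 | 48 | 0.59 | 66% |
| 0.7 | 0.51 | 71 | 0.49 | 82% |

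**The case against.** The strongest objection is that the lists in section 2.9.2.2 are outcome times, not a full sampling schedule. Creatinine and SBE prove it: both appear there with post-operative times only, yet both have a pre-operative value elsewhere in the article. The schedule itself is in Figure 1, whose legend includes NGAL and cystatin C and which is not shown. This stands. A reader might infer that no baseline NGAL or cystatin C is taken at all. The documents do not support that; they show only that the endpoint text names none. The contrast with acetate, where a pre-operative time is spelled out, is suggestive and no more.

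A reader might also infer that the acid-base series has no pre-operative reading. That is wrong for SBE by the definition of the primary endpoint. For the other gas analytes, a sample is drawn before anaesthesia and more are drawn before reperfusion.

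A third tempting reading is that treatment effects on these markers could not be told apart from pre-existing differences. Allocation is randomised, so the comparison of post-operative levels is unbiased. Its standard error already contains chance imbalance, and the type I error is not inflated. The 20% figure describes how often the arms start apart, not how often the result misleads.

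It is also fair to say that section 2.1 promises only to compare levels, which post-operative samples allow, and that a covariate is often settled in an analysis plan, which may exist. Both stand. They leave untouched the question of whether the sample is taken, which must be fixed before surgery.

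**Conclusion.** The point holds in limited form. For NGAL and cystatin C, the visible text gives no pre-operative value, and 0 h cannot stand in for one. If Figure 1 is silent too, the cost is precision (16% to 49% of the variance for an assumed r of 0.4 to 0.7) and the loss of within-patient change. Validity is not at stake.

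For creatinine and the acid-base series, the pre-operative value is already obtained or nearly so. There the point is only that the comparisons in section 2.11, as stated, do not use it. The primary endpoint and the sample size are unaffected.

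The size of the gain rests on correlations that the documents do not supply. With a low r it would be small.

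**What to change.** 1. Check Figure 1. If it already shows pre-operative NGAL and cystatin C, say so in section 2.9.2.2. If not, add a pre-operative time for both, in the text and in the figure. Assay them on the pre-operative draw already made for acetate; all three are specified as serum measurements.
2. List the pre-anaesthesia gas as the baseline for pH, bicarbonate, lactate and chloride as well as SBE. Derive a baseline effective SID from the same time point, with Mg if available.
3. State that the post-operative creatinine, cystatin C, NGAL, acid-base and effective SID series will be compared between arms with the pre-operative value as a covariate.

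The cost is at most 72 NGAL and 72 cystatin C assays on blood already drawn, plus the change of wording. The acid-base baselines are close to free. The number of patients, the treatment and the primary endpoint do not change.

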**Discussion:**

Metabolic acidosis is common perioperatively, potentially leading to decreased renal blood flow and reduced glomerular filtration rate. The use of balanced solutions can prevent hyperchloremic metabolic acidosis, thereby avoiding AKI in some patients. However, during liver transplantation, when well-functioning liver metabolism is lacking, the organic anions in conventional balanced solutions may remain strong anions and thus fail to maintain the acid-base status, but no solid clinical evidence exists now. This study will, for the first time, provide evidence on the relative effects of BRS vs. ARS on acid-base status and renal injury in patients undergoing liver transplantation.

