## Background

1.

Acute kidney injury (AKI) is a common complication following liver transplantation, occurring in 29%–60% of pateints (1–4). Once it develops, regardless of the severity of AKI, it is significantly associated with increased mortality (5). A long-term cohort study conducted by the National Institute of Diabetes, Digestive and Kidney Diseases showed that, compared with patients with normal renal function, those with AKI had a hazard ratio of 1-year mortality up to 3.59 (6). The development of AKI is due to multiple factors (7–14), one of which is intraoperative and postoperative infusion of supraphysiologic chlorinated liquids (15).

During liver transplantation, fluid therapy, including crystalloids and colloids, is considered the cornerstone of perioperative management to maintain normal blood volume and preserve renal perfusion (15). The RELIEF study shows that patients undergoing liver transplantation and other major abdominal surgeries had an average fluid infusion of 3,500 ml intraoperatively and 6,146 ml within 24 h after the operation, respectively, and most of the intravenous fluids are crystalloid (16, 17).

However, the ideal crystalloid during liver transplantation remains uncertain (18). By now, normal saline (NS, 0.9% sodium chloride) is most frequently used (19, 20). Nevertheless, the chloride concentration of NS (154 mmol/L) is significantly higher than that of plasma (94–111 mmol/L), which may lower plasma strong ion difference (SID), leading to metabolic acidosis and impaired renal perfusion (21, 22). A possible alternative is balanced solution (chloride limited crystalloid) (23), which, as shown in the SMART trial, could reduce adverse kidney events in critically ill patients when compared with NS (24).

In practice, the most commonly used balanced crystalloids are buffered with organic anions, such as lactate, acetate, or malate, all of which require liver metabolism to increase SID (25). During liver transplantation, liver metabolism is suspended during the anhepatic phase and severely compromised during the early neohepatic phase (26), thus organic anions buffered solution can not function properly, thereby inducing metabolic acidosis.

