On the contrary, bicarbonated Ringer's solution (BRS), introduced 11 years ago, directly replaces chloride with bicarbonate. It can increase SID regardless of liver metabolism. Previous pharmacokinetic studies showed that BRS could correct metabolic acidosis faster than lactated or acetated Ringer's solution (ARS) in shock models (26). Taken together, compared with conventional organic anion buffered balanced solutions, BRS may better maintain acid-base status during liver transplantation, but no evidence exists in the literature.

In this study, we aim to compare the effect of BRS and ARS on acid-base status and renal function in patients undergoing liver transplantation. The results of this study could also provide data to power a confirmatory Phase III study in the future.

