### Data management, sample size and statistical analysis

2.11.

The principal investigator will be responsible for data management, safety, privacy, and quality. The reporting and presentation of this trial will follow the CONSORT guidelines (29). Based on the principle of intention to treat (ITT), a full-analysis set (FAS) will be performed on the population with outcome reporting. FAS will be used for the analysis of baseline characteristics and main therapeutic interventions. The safety set (SS) will include all enrolled patients to assess the safety profile of the study intervention.

According to the previous study (30) and our unpublished data, the change of SBE during operation is approximately −2 mmol/L with a standard deviation of 2.5 mmol/L in patients receiving ARS. We estimated that a sample size of 72 participants (36 per group) could provide 80% power at a two-sided alpha level of 0.05 to detect ≥1.7 mmol/L increase in the primary endpoint results from the use of BRS with a potential loss of 5% recruitments.

Descriptive statistics will be used to assess any marked baseline differences in demographics or outcome measures between the two groups. Comparisons of binary outcomes will be expressed as relative risk with 95% confidence intervals and comparisons of continuous outcomes as mean differences together with 95% confidence intervals. Comparisons will be made using *t*-test and ANOVA for repeated-measures or Wilcoxon rank-signed test and Kruskall-Wallis according to the underlying distribution for continuous data and Chi-square or Fisher's exact *T* test for categorical data, as appropriate. Two-sided 5% significance levels will be used to identify statistically significant results. All confidence intervals reported will be 95% confidence intervals.

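### The secondary endpoint eSID has no acetate term, so retained acetate is left inside the computed SID and the endpoint could hide a true difference between the arms

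*Protocol article*

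**What the plan says.** The Protocol article, Part II: Renal function-related measures (2.9.2.2), gives a complete formula: "Effective SID (eSID = [Na^+^] + [K^+^] + [Ca^2+^] + [Mg^2+^]-[Cl^−^]-[Lac", ending with the lactate term. It is to be calculated "at 5 min post reperfusion of the donor liver, 0, 6, 12, 24 and 48 h post operation".

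The rationale for the trial is stated in terms of the same variable. Background says that conventional balanced crystalloids are buffered with organic anions "such as lactate, acetate, or malate, all of which require liver metabolism to increase SID". Of the bicarbonated solution (BRS) it says: "It can increase SID regardless of liver metabolism". The Discussion part of the abstract says that, without good liver metabolism, "the organic anions in conventional balanced solutions may remain strong anions and thus fail to maintain the acid-base status". The main Discussion (section 3) repeats the argument.

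Acetate is measured. Part I: Process measures (2.9.2.1) lists "Serum acetic acid concentration before operation, 5 min post reperfusion of the donor liver, 0, 6, 12, 24 and 48 h post operation". Nothing in the article links that measurement to the SID calculation.

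**The concern.** The formula subtracts one organic strong anion, lactate, but not the one that differs between the randomised fluids. Acetate still circulating is therefore handled as if it had already been converted to bicarbonate, and the trial's hypothesis is that during liver transplantation this conversion fails.

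What is at stake is the reading of one named secondary endpoint. The more acetate is retained, the larger the error. A result of no difference in eSID could then be taken as evidence against the proposed mechanism, or as conflicting with the SBE and bicarbonate results, when it came only from the way SID was calculated.

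**Working it through.** **The plan's own figures.** The article states no target, SD or expected value for eSID, so there is none to reproduce. Its one sample-size figure concerns SBE. It assumes a change "approximately −2 mmol/L with a standard deviation of 2.5 mmol/L in patients receiving ARS", a difference of 1.7 mmol/L, two-sided alpha 0.05, 80% power and 5% loss. By the normal approximation:

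- n per arm = 2 × (1.96 + 0.842)² × 2.5² / 1.7² = 33.9, rounded up to 34.
- 34 / 0.95 = 35.8, rounded up to 36 per arm, or 72 in total.

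This agrees with the article and does not involve the SID formula.

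**What the formula does with acetate.** Write S for the protocol formula and A for serum acetate, which carries one negative charge per molecule. On the protocol's own account of acetate, the SID that reflects the mechanism is S − A. The error in S is therefore A: 1 mmol/L for each mmol/L of acetate.

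Illustration with assumed values (Na 140, K 4, Ca 1.1, Mg 0.8, Cl 106, Lac 4 mmol/L; none is from the document): S = 140 + 4 + 1.1 + 0.8 − 106 − 4 = 35.9.

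| Acetate (mmol/L, assumed) | Protocol formula | With acetate subtracted |
|---|---|---|
| 0 | 35.9 | 35.9 |
| 2 | 35.9 | 33.9 |
| 5 | 35.9 | 30.9 |

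The protocol formula returns the same number whatever the acetate level.

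**Effect on the comparison.** Taking BRS minus ARS, the difference in S equals the difference in (S − A) minus (mean A in ARS − mean A in BRS). If acetate is higher in ARS, the computed advantage of BRS is too small by exactly that excess. In the special case of equal cations, chloride and lactate in both arms, and acetate present only in ARS, the computed difference is 0 while the acetate-corrected difference is A.

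**When it matters.** Background says that liver metabolism is suspended in the anhepatic phase and severely compromised early in the neohepatic phase. Retained acetate should thus be greatest at 5 min post reperfusion and 0 h. Study fluid continues for 48 h after operation (2.7), so the error at later times need not be zero.

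**Size, under assumptions.** The document gives no serum acetate values, and the fluid compositions are in Supplementary Table S1, which is not at hand. Assume acetate content of 24–28 mmol/L, a volume of 3.5 L, a distribution volume of 14–20 L, and 10–50% unmetabolised at sampling. The 3.5 L is the average intraoperative infusion that Background cites for liver transplantation and other major abdominal surgery, not an ARS volume for this trial.

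Overstatement = content × volume × unmetabolised fraction / distribution volume:

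- low: 24 × 3.5 × 0.10 / 20 = 0.42 mmol/L
- middle: 28 × 3.5 × 0.20 / 20 = 0.98 mmol/L
- high: 28 × 3.5 × 0.50 / 14 = 3.5 mmol/L

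**The case against.** **The mechanism can be seen elsewhere.** A reader might infer that the trial cannot show the mechanism it tests. The document does not support that. The primary outcome is stated as follows: "The primary outcome measure is the change of SBE during the operation", and the SID formula does not enter it. Arterial pH, SBE and HCO3 are listed at the same six times as eSID, and serum acetate at those times and before operation. Retained acetate with low bicarbonate would show there. This objection stands in full and confines the point to eSID. Whether eSID is the endpoint nearest the mechanism is also a matter of opinion, since serum acetate measures the anion itself.

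**The error need not fall in one arm only, nor always towards no difference.** Without the composition table, BRS cannot be assumed free of other anions that the formula ignores. Acetic acid is scheduled before operation and is not restricted to one arm, so the plan does not treat it as zero outside ARS. The direction of the net SID contrast also depends on the sodium and chloride of each fluid. This stands too: an excess mainly in ARS is what the rationale leads one to expect, but it is not established.

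**The size is assumed.** The range is about eightfold, every input other than the volume is outside the document, and the volume is borrowed from other surgery. It is also tempting to set the range against 1.7 mmol/L, but that is the design difference for SBE, a different variable.

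**Acetate is already reported, and a SAP may exist.** Neither answers the point. A separate listing does not correct a derived variable that ignores acetate, and this is not a detail left open for a SAP: the article fixes the full formula.

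**Conclusion.** The point holds for the eSID endpoint alone. The formula is insensitive to retained acetate, which the protocol itself calls a strong anion that does not raise SID, and it overstates SID by 1 mmol/L per mmol/L retained. That relation is arithmetic and needs no assumption beyond the protocol's own account of acetate.

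That the excess lies mainly in ARS and mainly at the first two sampling times is an expectation drawn from the rationale. That it masks a true difference is a possibility, not a demonstrated result. The size cannot be fixed from the document; 0.4 to 3.5 mmol/L is an illustration resting on the assumed inputs above.

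The primary analysis, the sample size and the other acid-base endpoints stand as they are. This is a correction worth making to one secondary endpoint, not a defect in the trial's main test.

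**What to change.** Before arm-level data are examined, define SID in both arms as [Na] + [K] + [Ca] + [Mg] − [Cl] − [Lac] − [acetate], taking acetate from the serum acetic acid measurement at the matching time (5 min post reperfusion, 0, 6, 12, 24 and 48 h). Report the present formula alongside it, so that the effect of the extra term is visible.

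The cost is one term in a derived variable. No new samples, patients or changes in care are needed. The one drawback is that the corrected SID will be missing wherever the acetate value is missing, so the number of patients contributing at each time should be shown for both versions.
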